### Questionnaire to be utilized in this study

Researchers use Kessler Psychological Distress Scale (K10) from Kessler et al., (2002), is a 10-item
questionnaire assessing anxiety and depressive symptoms over the past four
weeks, with scores ranging from 10 to 50. A score under 20 suggests good mental
health, while scores from 20 to 50 indicate varying levels of mental disorder
severity ( Andrew & Slade, 2001;
Kessler et al., 2002). Coping
self-efficacy questionnaire will be adapting from Chesney et al. (2006), measuring confidence in coping
behaviors, such as problem-focused coping and managing emotions. Respondents
rate their confidence on an 11-point scale, and higher scores indicate greater
coping self-efficacy, with good reliability and predictive validity for
decreased psychological distress and increased well-being. and Knowledge,
attitude, and practice HIV voluntary and counselling testing (K-A-P VCT) from
Addis et al., (2013) is consists of
15 questions assessing participants’ knowledge, attitude, and practice
regarding VCT services. Knowledge is measured through correct answers, attitudes
are evaluated using a 5-item scale, and practice is determined by a single
question about previous use of VCT services.

Questionnaire will be adapting from Addis et al. (2013).

### Statistical analysis

Demographic characteristics and predictor variables were summarized as
frequencies (n) and percentages (%) for categorical data, and means with
standard deviations for continuous data. Descriptive statistics, including
percentage and frequency distributions, are presented using tables and charts.
Chi-square tests and independent t-tests (or ANOVA where appropriate) were used
to compare socioeconomic and baseline characteristics between the two study
groups.

For inferential analysis, the association between each independent variable and
the outcome variable was initially examined using binary logistic regression.
The primary outcomes—psychological distress (K10), HIV prevention
knowledge and practices (KAP VCT), and communication self-efficacy
(CSE)—were analyzed using Generalized Estimating Equations (GEE) to
account for repeated measures and within-subject correlations over time. The GEE
model included main effects of group and time, as well as their interaction term
(group × time), to evaluate differential changes between intervention and
control groups across three measurement points (baseline, post-intervention, and
4-week follow-up). Adjusted odds ratios with 95% confidence intervals are
reported.

Missing data will be handled under the missing at random (MAR) assumption
inherent in GEE, and sensitivity analyses will be conducted to assess the
robustness of findings.

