**Results:**

The analysis of the data will be conducted utilizing the generalized
estimation equation, with a confidence interval set at 95%. Significant
differences, both between and within groups, will be identified at a
threshold of P<.05. The findings of this study highlight the efficacy of
a mobile educational program in enhancing mental health and preventing HIV
within the deaf community. Furthermore, the outcomes of this research will
augment existing knowledge regarding psychological distress, HIV prevention
practices, and coping self-efficacy among individuals who are deaf.

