### Sample size

The sample size was determined using the software Based on an a priori power
analysis (G*Power 3.1) ( Faul et al., 2007). An *F*-test (ANOVA: repeated
measures, within-between interaction) was selected as the statistical test,
assuming two groups (intervention and control). The analysis used a conventional
alpha level (α) of 0.05, a statistical power (1 - β) of 0.95, and
a small to medium effect size (f = 0.20), in line with guideline from ( Chow et al., 2002). Based on the
parameters, the minimum required sample size was calculated to be 66
participants (33 per group).

 To account for potential attrition, a 20% dropout rate was anticipated, as
supported by previous studies ( In et al., 2020; Suresh & Chandrashekara, 2012). The adjustment led to an additional 7 participants per group,
resulting in a final target sample size of 40 participants per group, or total
of 80 deaf participants for this study. The final analysis will be conducted
using Generalized Estimating Equations (GEE) to account for the correlated
nature of repeated measures over time and provide robust estimates of
intervention effects.

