### Outcome MHealth KaPi Program

Increase in physical and psychological capability of HIV voluntary counseling and
testing.

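### Three primary outcomes share an unadjusted P<.05 in a trial sized for one test, and the sections disagree on what the outcomes are

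*Protocol article*

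**What the plan says.** **Primary outcomes.** The Statistical analysis section starts its list with "The primary outcomes—psychological distress (K10), HIV prevention" and continues with "knowledge and practices (KAP VCT), and communication self-efficacy". Each outcome goes into a GEE model with group, time and group × time over three measurement points. None is named as the lead outcome.

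**Significance.** The Abstract (Results) says that significant "differences, both between and within groups, will be identified at a" "threshold of P<.05".

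**Sample size.** A repeated-measures F-test ("measures, within-between interaction) was selected as the statistical test") with alpha 0.05, power 0.95 and f = 0.20 gives 66 participants, raised to 80 for 20% dropout.

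**Instruments.** The questionnaire section describes a scale on which higher scores mean greater "coping self-efficacy, with good reliability and predictive validity for" lower distress and better well-being. In the KAP-VCT, knowledge is counted from correct answers, while attitudes "are evaluated using a 5-item scale, and practice is determined by a single" question on past use of the service.

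**Outcome section.** The section headed Outcome MHealth KaPi Program gives only "Increase in physical and psychological capability of HIV voluntary counseling and" testing.

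**The concern.** There are two linked problems.

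First, three primaries are each judged at 0.05, with no lead outcome, alpha split, testing order or requirement that all succeed. Nothing in the article stops a claim of effect that rests on whichever primary reaches significance. The same threshold is attached to within-group differences. A before-after change in the app arm is not a comparison with control. In a non-randomized trial it can reflect time, repeated testing or regression to the mean.

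Second, the sections do not agree on which outcomes are primary or how many there are. With that open, the set can be settled after the data are seen, and no error rate can be attached to the trial's conclusion.

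**Working it through.** **1. The plan's own figure.** Inputs from Sample size: two groups, f = 0.20, alpha 0.05, power 0.95. From Statistical analysis: m = 3 measurement points. Assumed, because the article does not give them: within-person correlation ρ = 0.5 and sphericity (ε = 1).

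- λ = f² × N × m / (1 − ρ) = 0.04 × 66 × 3 / 0.5 = 15.84
- df1 = (2 − 1)(3 − 1) = 2; df2 = (66 − 2)(3 − 1) = 128
- Power from the noncentral F at alpha 0.05 = 0.9504

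The stated N = 66 is reproduced. It is the number for one outcome tested once at 0.05.

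**2. Familywise error if any one significant primary counts as success.** One between-group test per outcome at 0.05. If independent, the rate is 1 − 0.95^k. Correlated values are simulated from k equicorrelated two-sided z-tests (500,000 draws).

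| Tests | Independent | Corr. 0.3 | Corr. 0.5 | Corr. 0.7 | Corr. 0.9 |
|---|---|---|---|---|---|
| 3 (KAP-VCT as one score) | 14.3% | 13.6% | 12.5% | 10.9% | 8.4% |
| 4 (knowledge and practice separate) | 18.6% | – | – | – | – |
| 5 (attitude added) | 22.6% | 20.8% | 18.3% | 14.9% | 10.2% |

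Within-group tests are left out, since they do not estimate the intervention effect.

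**3. Power if three primaries are kept.** Same formula at the Bonferroni level 0.05/3 = 0.0167, where the familywise error is 1 − (1 − 0.0167)³ = 4.9% if independent.

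- N = 66: 0.886
- N = 80 (no dropout; λ = 0.04 × 80 × 3 / 0.5 = 19.2): 0.946
- N = 64 (80 less the anticipated 20%): 0.874
- N for 0.95: 82, that is 41 per group, or 41 / 0.8 = 51.25, so 52 per group before dropout

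Holm rejects whatever Bonferroni rejects, so these powers are lower bounds for Holm.

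**4. The outcome lists side by side.**

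| Section | Self-efficacy | KAP-VCT | Other |
|---|---|---|---|
| Statistical analysis | communication | knowledge, practice | K10 |
| Questionnaire | coping | knowledge, attitude, practice | K10 |
| Abstract (Results, Conclusion) | coping | HIV prevention practices | distress |
| Results (main text) | coping | knowledge, attitudes, practices | distress |
| Outcome MHealth KaPi Program | – | – | capability for VCT only |

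No listed instrument measures communication self-efficacy, and none is said to measure capability for VCT.

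**The case against.** The strongest reply is that the article never says one significant result proves the app works. The Abstract only says where significant differences will be identified, Statistical analysis evaluates the intervention through group × time, and the Abstract's Conclusion expects gains on distress, HIV prevention and coping self-efficacy together. If all primaries had to succeed, there would be no inflation. This stands in part. A reader might infer a stated rule under which any one positive primary, or a before-after change alone, shows effectiveness; no such rule is written. But the expected joint pattern is not a decision rule either, so the inflation is conditional rather than excluded.

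Other stronger readings also go beyond the text:

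- Five primary scores is a count combined from the questionnaire section and the main Results. The analysis section itself supports three outcomes, or four if knowledge and practice are split.
- Separate tests at each follow-up are not stated; the interaction can be one test per outcome.
- The naming conflict does not itself raise the error rate. The number of tests does. Each single test keeps its 5%.

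It is also fair that the abbreviation CSE fits coping self-efficacy, so that mismatch may be a one-word slip, that the trial is described as assessing preliminary effectiveness, and that multiplicity detail can sit in an analysis plan not shown here. The absence of a procedure alone would therefore be no finding. What the article does state remains: plural primaries, the 0.05 threshold applied to within-group change, and sections that name different outcomes.

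**Conclusion.** The point holds in conditional form. If any one significant primary is read as success, the familywise false-positive rate for between-group tests is 8.4% to 14.3% over correlations from 0.9 to 0, with about 12.5% at correlation 0.5. The coping scale is described as predicting lower distress, so some correlation is likely and 14.3% is better read as the upper end. Testing the KAP-VCT parts separately gives 18.6% for four scores or 22.6% for five, if independent. Even at correlation 0.9, three outcomes do not return to 5%.

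The contradictions in the outcome list need no assumption and stand on the text. So does the attachment of significance to within-group change. The power figures rest on the assumed within-person correlation of 0.5 and sphericity, and describe the ANOVA used for planning rather than the GEE model.

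**What to change.** 1. In Statistical analysis, keep the three named primaries, define one score for each (for KAP-VCT, say which), test each by its group × time contrast, and apply Holm at a familywise 0.05. Alternatively, the sponsor names one primary and makes the others secondary. Which one is the sponsor's choice, because the Objective gives mental health and HIV prevention equal place.
2. In the Abstract, remove within-group significance as evidence of effect and report within-group change descriptively.
3. In Statistical analysis, change communication to coping self-efficacy.
4. Make the outcome section, the questionnaire section, Statistical analysis and the main Results give the same outcome list, including whether attitude belongs to it.
5. If three primaries stay, restate per-outcome power in Sample size: at 0.05/3, about 0.89 at N = 66 and 0.95 at N = 80, with the assumed correlation and sphericity stated.

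The edits are short, and the registered outcomes should be checked against the final list. The price is a stricter threshold per outcome and a somewhat lower stated power. Keeping 0.95 per outcome at the Bonferroni level would need 82 analysed participants.

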## Methods

This quasi-experimental study follows a non-randomized controlled trial design, in
which participants are assigned to either the intervention group, receiving the
mobile health KaPi program, and the control group, receiving standard educational
materials in the form of e-books. To minimize potential bias, participants will be
blinded to their group allocation; they will not be informed whether they are
receiving the intervention or serving as part of the control group. Efforts will be
made to ensure that the delivery of content appears comparable across groups to
prevent participants from discerning their allocation. Data collection took three
months from the first intervention given. To ensure that the intervention carried
out is in accordance with the standards, the researcher using the Standard Protocol
Items as a guide. The study will adhere to the Standard Protocol Items:
Recommendations for Interventional Trials (SPIRIT) guidelines ( Chan et al., 2016), the Consolidated Standards
of Reporting Trials (CONSORT) criteria ( Schulz et al., 2010), and the recommendations set forth by the Consolidated
Standards of Reporting Trials of Electronic and Mobile Health Applications and
Online Telehealth (CONSORT-EHEALTH) ( Eysenbach et al., 2011). Participation in the study was voluntary, and no financial
compensation was offered. To ensure the accuracy and validity of this study, we will
take strategic steps to minimize bias. The study will start with clear, testable
objectives and hypotheses, and random sampling will be used to ensure
representativeness. Data will be collected using valid, reliable instruments and
standardized procedures. A blind or double-blind design will be implemented to
reduce bias from both researchers and participants. Data analysis will follow
appropriate statistical methods to avoid misinterpretation. The research process
will be transparently reported, with methods and results available for replication.
Peer review and potential replication by other researchers will further confirm the
findings, ensuring the study produces valid, unbiased results.

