### Study design

This study will employ a quasi-experimental, non-randomized controlled trial
design with single blinding applied to participants. The control group will
receive standard therapy, while the intervention group will receive the mobile
health program. A parallel assignment approach will be used, reflecting the
structure of health services research. This study corresponds to a Phase
2–3 trial, aiming to evaluate both the feasibility and preliminary
effectiveness of the intervention. One or two (experimental group) receives the
Mobile health KaPi Program intervention under test and the other (comparison
group or control) receives the standard e book/leaflet. Then follow up on the
two or more groups to see if there are any differences in the results. The
results of the study and subsequent analysis are used to assess the
effectiveness of the intervention mobile health application. Quasi-experimental
are the most rigorous way to determine if there is a causal link between
interventions and outcomes ( Polit and Beck, 2017).  Figure 1 provides an
overview of the study design. The choice of this experimental design is grounded
in its robustness and efficacy ( Creswell, 2016).

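### The arms are not randomised, but the stated GEE names only group, time and group × time, so differences that predict change stay in the effect reported as adjusted

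*Protocol article*

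**What the plan says.** The opening of Methods states: "This quasi-experimental study follows a non-randomized controlled trial design, in" which participants go to the KaPi programme or to e-book material. The Abstract and Study design also declare a non-randomised design. No allocation rule, matching or stratification is given.

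Statistical analysis says the GEE "model included main effects of group and time, as well as their interaction term". The interaction is there to compare change between arms over three measurement points. For baseline comparability, "Chi-square tests and independent t-tests (or ANOVA where appropriate) were used", with no stated consequence for the model. Separately, the association of each independent variable with "the outcome variable was initially examined using binary logistic regression". These regressions are not linked to the GEE. The section then reports adjusted odds ratios without saying what they are adjusted for.

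Three other statements bear on the point. The eligibility section presents the inclusion and exclusion criteria as controlling confounding. Study design says quasi-experiments "are the most rigorous way to determine if there is a causal link between" interventions and outcomes. Methods says the study starts with clear "objectives and hypotheses, and random sampling will be used to ensure" representativeness, while Recruitment describes contact through the leadership of one NGO.

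**The concern.** In a non-randomised comparison, the arms may differ in characteristics that influence how much a participant improves. Group × time compares changes, so it takes out a difference in starting level that stays constant. It does not take out a difference in trajectory caused by, for instance, age or socioeconomic position. Run with the terms named, the model attributes such a difference to the programme.

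The group × time term carries the effectiveness claim for all the primary outcomes (K10, KAP VCT and CSE). A reader who sees adjusted estimates and a statement that the design is the strongest route to causation would take the result as causal evidence. The stated analysis does not provide that.

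**Working it through.** **1. The plan's own figure.** Sample size uses a repeated-measures ANOVA interaction with f = 0.20, α = 0.05, power 0.95 and two groups. Taking m = 3 measurements (Statistical analysis) and assuming correlation ρ = 0.5 and no sphericity correction, λ = f²·N·m/(1 − ρ) = 0.04 × 66 × 3 / 0.5 = 15.84 on 2 and 128 degrees of freedom. Power is 0.9504, so N = 66 (33 per arm) reproduces. The target after the dropout allowance is 40 per arm. I use 33 and 40 per arm below.

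**2. What the baseline tests can detect.** Two-sided t-test, 40 per arm, α = 0.05:

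| Imbalance between arms | Power |
|---|---|
| 0.2 SD | 14% |
| 0.3 SD | 26% |
| 0.4 SD | 42% |
| 0.5 SD | 60% |

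For binary characteristics, power is 45% for 50% v 30% and 27% for 50% v 35%. A non-significant result therefore says little about balance.

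**3. Size of the bias (assumed inputs).** Let a covariate X differ by d SD between arms, and let change in outcome depend on X by g SD per SD. With no true effect, the group × time estimate on a linear scale is biased by about d × g. The documents give neither d nor g.

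With d = 0.5 and g = 0.4, the bias is 0.5 × 0.4 = 0.2 SD. With ρ = 0.5, the SD of change is √(2 × (1 − 0.5)) = 1, so the standard error of the contrast is √(2/n):

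- n = 40: SE = 0.224, shift = 0.2/0.224 = 0.894. Rejection rate = Φ(0.894 − 1.96) + Φ(−0.894 − 1.96) ≈ 14.5%.
- n = 33: SE = 0.246, shift = 0.2/0.246 = 0.812. The same formula gives ≈ 12.8%.

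Exact t calculations give 14.3% and 12.6%. The range is about 13–15% against a nominal 5%.

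**4. Simulation of the stated model and two repairs.** Linear GEE, exchangeable correlation, 40 per arm, three time points, true effect zero, 400 runs per scenario. Each cell gives the mean group × time estimate in SD and the rejection rate:

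| d, g | Stated terms | Plus X as main effect | Plus X and X × time |
|---|---|---|---|
| 0.4, 0 | −0.005; 4.5% | −0.005; 4.5% | −0.007; 5.2% |
| 0.4, 0.3 | 0.123; 7.5% | 0.123; 7.5% | 0.002; 5.5% |
| 0.4, 0.5 | 0.211; 15.8% | 0.211; 15.8% | 0.004; 5.8% |
| 0.5, 0.5 | 0.230; 16.0% | 0.230; 16.0% | −0.027; 7.5% |

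Monte Carlo error of the rejection rates is about 1 to 2 points. Three things follow. A covariate that affects only level (g = 0) causes no bias. One that affects change does. Adding it as a main effect alone leaves the bias untouched in a linear model, so the usual quick repair would not work.

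**5. The other stated safeguards.** Eligibility restriction applies to both arms alike, so it cannot balance them. One-at-a-time regressions on the outcome do not examine differences between arms. The sensitivity analyses appear in the sentence on missing data, with no content given.

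**The case against.** The text says the GEE included these terms. It does not say that it contained nothing else. Initial regressions followed by adjusted odds ratios fit a plan to screen variables and then adjust, and a condensed article may leave the covariate list to a fuller document. A reader might infer that the trial has decided against adjustment, and the article does not support that. What stands is that the model terms are spelled out, none is a covariate, and the label adjusted has nothing behind it in this document.

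It would also go too far to call the baseline p-values the sole safeguard, since restriction and predictor screening are stated. Neither balances the arms or corrects an imbalance.

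The section reports odds ratios, whereas the results on level differences and main effects are exact only on a linear scale. That limit is accepted, and no figure is offered on the logit scale.

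The size of bias is assumed. A larger illustration is tempting: a spurious 0.3 SD would push the rejection rate to about 23–27%. With a slope of 0.4 that needs an imbalance of 0.3/0.4 = 0.75 SD, which the baseline t-test would detect with about 91% power, so I do not rely on it.

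Finally, non-randomisation is declared openly and Study design speaks of preliminary effectiveness. That tempers the claim, but the causal sentence in the same section works against it.

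**Conclusion.** The point holds. With non-random allocation, a GEE with the terms named leaves confounding of change in the effect estimate, and the article gives no adjustment to justify its label. The low power of the baseline tests (26%, 42% and 60% at 0.3, 0.4 and 0.5 SD) rests only on 40 per arm and α = 0.05. The rejection rate of about 13–15% rests on assumed values: a 0.5 SD imbalance, a slope of 0.4 SD and a correlation of 0.5. Simulated scenarios with confounded change ranged from 7.5% to 16%.

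The documents do not show that the arms will in fact differ, nor that a stable baseline difference in level biases group × time. Random sampling concerns representativeness. It is not a claim of random allocation and gives no protection against confounding. It sits badly with recruitment through NGO leaders but is not strictly excluded by it. The statement that this design is the most rigorous route to causation is wrong for a non-randomised comparison.

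**What to change.** **Statistical analysis, model.** Pre-specify about three or four baseline demographic and socioeconomic variables that the trial collects, such as age, gender and a socioeconomic measure. They should not be chosen by baseline or univariable p-values. Enter them so that they act on change, by one of three routes:

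- covariate × time terms in the GEE;
- a model of the post-baseline outcomes adjusted for the baseline value and the covariates;
- propensity-score weighting.

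State which variables lie behind the adjusted estimates. Previous use of VCT is itself the practice outcome (the questionnaire section defines practice by that single question), so use it as a covariate only for the other outcomes. Use Gerkatin branch only if it is recorded and not aliased with group.

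**Statistical analysis, baseline table.** Report standardised differences in place of p-values.

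**Study design and Methods.** Remove the most-rigorous claim and describe effects as adjusted associations from a non-randomised comparison. Reconcile random sampling with the recruitment route.

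**Cost.** Mostly wording. With three time points, each single-degree-of-freedom covariate costs 1 + 2 = 3 parameters if time interactions are used, so four covariates add 12. With 66–80 participants the set must stay small. The baseline-adjusted and weighted routes cost fewer. Randomising instead would be a redesign of the trial and is not part of this analysis fix.

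### If the VCT practice item means ever-use and is modelled as binary, its group × time odds ratio is 1 under equal new testing only when the non-randomised arms start at the same level

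*Protocol article*

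**What the plan says.** The Study design section is explicit about allocation: "This study will employ a quasi-experimental, non-randomized controlled trial". Nothing in the Methods balances prior HIV testing between the arms.

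The Questionnaire section gives practice its own scoring rule, separate from knowledge and attitude: a single "question about previous use of VCT services". No look-back period is stated for it, although one is stated for the K10.

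The Statistical analysis section lists among the primary outcomes "knowledge and practices (KAP VCT), and communication self-efficacy". These are analysed by GEE over three measurement points, baseline included. The "model included main effects of group and time, as well as their interaction term" ("group × time), to evaluate differential changes between intervention and" control groups). The only effect measure named is the odds ratio: "Adjusted odds ratios with 95% confidence intervals are" to be reported. No step restricts the practice item to people not yet tested, or redefines it as testing since baseline.

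**The concern.** A question about previous use is cumulative. Someone who has used VCT remains a previous user, so prevalence in each arm can only stay the same or rise. For such an item, the within-arm odds ratio over time depends on where the arm began as well as on how many people newly tested. Two arms with the same new-testing rate but different starting levels therefore have different odds ratios over time, and the interaction term reads the difference as an intervention effect.

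This is the only HIV behaviour that the Questionnaire section describes measuring, and the abstract anticipates better HIV prevention practices with the intervention. If the KaPi arm happened to be the less tested group, the analysis could support that claim when KaPi produced no more testing than the e-book. If it were the more tested group, a real gain could be hidden.

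**Working it through.** **Inputs.** From the article: 40 participants per arm, three visits, two-sided 5% level, and a background figure of 28.9% ever screened for HIV (Introduction). Not in the article, so assumed: each arm's baseline prevalence *p* and the share *h* of the untested who newly test, taken as equal in both arms. The plan states no figure for this item, so there is none to reproduce.

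**Formula.** Later prevalence is *p* + (1 − *p*)*h*. The within-arm odds ratio over time is then [1 + *h*(1 − *p*)/*p*]/(1 − *h*), which falls as *p* rises. The interaction odds ratio is the KaPi value divided by the control value. It equals 1 only if the two *p* are equal.

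**One case in full.** Take baseline 20% (KaPi) vs 40% (control), with 25% of the untested newly tested in both arms.
- KaPi: 0.20 + 0.80 × 0.25 = 0.40; odds 0.25 → 0.667; odds ratio 2.67.
- Control: 0.40 + 0.60 × 0.25 = 0.55; odds 0.667 → 1.222; odds ratio 1.83.
- Interaction: 2.67/1.83 = 1.45. With the arms reversed it is 0.69.

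**Range.** The last column is the simulated rejection rate of the baseline-to-follow-up contrast (logistic GEE, robust variance, 40 per arm, no true difference in uptake).

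| Baseline, KaPi vs control | Uptake in both | Within-arm odds ratios | Interaction odds ratio | False-positive rate |
|---|---|---|---|---|
| 28.9% vs 28.9% | 10% to 50% | equal | 1.00 | about 5% |
| 25% vs 33% | 10% | 1.44 and 1.34 | 1.08 | 5–6% |
| 25% vs 33% | 25% | 2.33 and 2.01 | 1.16 | about 7% |
| 25% vs 33% | 50% | 5.00 and 4.03 | 1.24 | about 7% |
| 20% vs 40% | 10% | 1.56 and 1.28 | 1.22 | about 8% |
| 20% vs 40% | 25% | 2.67 and 1.83 | 1.45 | about 14% |
| 20% vs 40% | 50% | 6.00 and 3.50 | 1.71 | about 18% |

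At 5% uptake there are few new events and the test is conservative: about 3% at both 25% vs 33% and 20% vs 40%. The joint two-degree-of-freedom group × time test at 20% vs 40% rejects in about 9–10% (uptake 15% then 25%) and 14–15% (30% then 50%).

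**Other meanings of equal.** Suppose both arms rise by 10 points from 20% and 40%. The odds ratios are (0.30/0.70)/(0.20/0.80) = 1.71 and (0.50/0.50)/(0.40/0.60) = 1.50, ratio 1.14. So an equal absolute rise is null on the risk-difference scale but not on the planned odds-ratio scale. With an equal share of the untested (the case in full above), the risk-difference interaction is (40 − 20) − (55 − 40) = +5 points.

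**Alternative target.** Among those answering no at baseline, the new-testing proportions are *h* and *h*: risk difference 0 and risk ratio 1, whatever the two baselines. Simulated rejection in the unequal-baseline cases was 5.1% to 5.6%.

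**The case against.** The strongest reply is that the premises are inferred. The article names one KAP VCT outcome from a 15-question instrument and does not say that the practice item gets its own model. It also says the questionnaire will be adapted, so the final wording could carry a recall window. If practice were folded into a summed score, or asked over a fixed period, this argument would not apply in this form. That stands, and the point is conditional on it. Still, practice has its own scoring rule, no window is given, and an odds ratio fits a binary item better than a score.

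The second reply concerns size. Both arms come from one NGO network in one district under one set of criteria, and nothing in the article points to a large gap. With 28.9% in both arms and 40 per arm, the standard error of the baseline difference is √(2 × 0.289 × 0.711/40) ≈ 10 points, so a 20-point gap is about two standard errors. This also stands: at an 8-point gap the distortion is small. It does not dispose of the point, because non-random allocation permits a systematic gap of unknown size. The planned baseline comparison would show a gap without correcting for it. Adjusting the odds ratio for covariates does not by itself help while earlier testers stay in a cumulative outcome.

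A reader might infer that the error rate for this item simply exceeds 5%. The documents do not support that, since it is about 5% when the arms start level. Nor is it right that no change of scale could help. That holds only if equal means an equal share of the untested; an equal absolute rise is null as a risk difference.

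**Conclusion.** The concern holds conditionally. It requires that the item means ever-use, that it is modelled as binary with the stated interaction and odds-ratio scale, and that the arms differ in underlying prior testing. The first two are the natural reading of the article but are not spelled out. The third is left open by the design.

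Under those conditions the bias is small at about 8 points of imbalance and material at about 20 points. Its direction favours whichever arm starts lower. Even at 20 points most trials of this size would not reach P<.05, so the more general harm is a distorted estimate.

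The point does not extend to K10, coping self-efficacy, knowledge or attitude, and it does not put the other primary analyses in doubt. It is worth correcting because the change is one of wording.

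**What to change.** In the Statistical analysis section, take the practice item out of the three-visit group × time odds-ratio model. Define its outcome as first VCT use after baseline among participants who answered no at baseline. Compare the arms by risk difference or risk ratio with a 95% interval, adjusted for baseline characteristics that are already collected and are named before analysis (the article names no adjustment set). Report previous use at baseline by arm descriptively only. State in the Questionnaire section whether the item is ever-use or has a recall window.

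The cost is wording only, with no new data. There are two downsides. The denominator falls to about 80 × (1 − 0.289) ≈ 57, or about 57 × 0.80 ≈ 46 after the anticipated 20% dropout, if 28.9% were tested before; those left out carry no information on first testing. The never-tested may also differ between non-randomised arms, for example if those still untested in the more-tested arm are harder to reach. Residual confounding therefore remains and should be acknowledged.
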